### Feasibility and Engagement Outcomes

We will assess several metrics to gauge the feasibility of evaluating the intervention in a larger-scale trial. Key metrics include completion rates for surveys and interviews (retention and engagement), instances of lost or damaged phones or watches (technology use barriers), and participant engagement with app features, such as completing the e-book for smoking cessation and setting and reviewing daily step goals. We will also characterize the frequency of photo uploads of daily step counts, completion of daily smoking status assessments, NRT adherence, completion of counseling sessions, and duration of smartwatch wear. These feasibility metrics will also be explored qualitatively by interviewing participants about their experiences with the intervention (ie, exit interview), such as their engagement with app features, ease of completing assessments, and any challenges encountered with study equipment.

### Sample Size Justification

The sample size of 60 participants was chosen based on recommendations for feasibility trials [104,105], which prioritize assessing study processes, recruitment, retention, and intervention engagement rather than detecting statistically significant effects. This sample size is sufficient to evaluate key feasibility metrics, such as recruitment rates (target: ≥5 participants/mo), retention (≥75% completion), and adherence to intervention components, which are critical for planning a fully powered randomized controlled trial. In addition, this sample size allows for preliminary comparisons between the HealthyCells and HealthyCells+ groups to explore trends in CO-verified smoking abstinence and changes in daily step counts.

### Analytic Plan

This analytic plan will focus on describing intervention feasibility. Feasibility indicators will include enrollment of all study participants within 12 months (≥5 adults enrolled/mo), retention of at least 75% of the participants at 8 weeks postquit date, achieving 20% smoking abstinence at 8 weeks postquit date (consistent with NRT and behavioral support standards) [104,105], and observing a meaningful 500 to 1500 [106,107] average daily step increase at eighth week postquit date. SAS (version 9.4; SAS Institute) [108] will be used for all statistical analyses, generating descriptive statistics to compare demographics, smoking status, and physical activity levels by treatment group. Group comparisons on participant characteristics and outcomes will use 2-tailed *t* tests for continuous variables and chi-square tests for categorical variables. Given the small sample size and pilot design (N=60), we will report all potential group differences with the α set at *P*<.20, following recommendations for pilot studies [109].

Smoking cessation will be analyzed in two ways: (1) an intention-to-treat analysis with missing data classified as smoking and (2) a completers-only analysis excluding participants with missing data. For physical activity outcomes, specifically the change in average daily step count from the baseline week to the eighth week postquit date, *t* tests will evaluate pre-post differences between groups. Days with <500 steps or <10 hours of watch wear time (indicating nonwear time or recording error) will be excluded. Participants must have at least 4 days of valid step count data to be included in the analyses.

Exploratory analyses will examine the association between physical activity and smoking cessation success using continuous and categorical approaches, with 6000 steps as the threshold for categorical analyses. Logistic regression analysis will evaluate the impact of average daily step count based on all postquit assessment weeks (5 wk in total) on CO-verified 7-day point prevalence abstinence at 8 weeks postquit date. In addition, participants will be categorized based on achieving a daily average of ≥6000 steps, allowing us to evaluate whether higher activity levels (≥6000 steps) are associated with greater cessation success. Finally, we will explore additional metrics, including the number of consecutive abstinent days and the frequency of meeting daily step goals. The analysis will examine these metrics as continuous and categorical variables to assess their association with smoking cessation rates.

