### Study Randomization

Participants will be stratified according to self-reported sedentary time at baseline (high: >8 h/d, medium: 4-8 h/d, and low: <4 h/d) assessed via the International Physical Activity Questionnaire [87]. Participants (n=60) will be randomized 1:1 in REDCap [85], and research staff will text each new participant a unique code (HealthyCells: 0101 and HealthyCells+: 0202) to access assigned app content.

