### Postintervention Assessment and Treatment Outcomes

At the eighth week postquit date, participants will complete a postintervention assessment via REDCap [85], answering questions similar to those in the baseline assessment to track changes in physical and mental health and health behaviors and to assess app impressions (Multimedia Appendix 1). A final semistructured interview will gather feedback on the app and suggestions for improvement (Table 1). The primary outcome for smoking cessation will be CO-verified, 7-day point prevalence smoking abstinence at 8 weeks postquit date, which will be assessed via smartphone-based self-report and a corroborating CO assessment. Expired CO is a valid indicator of smoking and cessation and compares favorably with cotinine and other biochemical measures [101]. Daily abstinence will be examined as a secondary outcome and defined as self-reported abstinence within the day combined with 2 breath CO sample submissions <6 ppm and identity verification. The number of days and consecutive days of CO-verified abstinence will be explored as additional outcomes. The other primary outcome will be the net change in average daily steps during the eighth week postquit date compared with average daily steps the week before the quit attempt (HealthyCells+ group only). Second, we will explore the number of total and consecutive days that ≥6000 steps were achieved as additional outcomes [102]. A valid day of observation for daily steps will be defined as (1) a smartwatch that was worn for at least 10 waking hours with (2) ≥500 steps taken within a day [103].

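### The planned group comparisons are unadjusted and leave out the randomisation stratum, which costs precision but not validity, and the 10-hour wear rule does not rule out a wear-time difference between arms

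*Protocol article*

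**What the plan says.** - **Tests.** The Analytic Plan says that "Group comparisons on participant characteristics and outcomes will use 2-tailed" t tests for continuous variables and chi-square tests for categorical variables. It names no covariate or stratum term and sets α at .20.
- **Step outcome.** The variable analysed is "specifically the change in average daily step count from the baseline week to the eighth week postquit date", compared between groups by t test. The section on postintervention outcomes defines it as the "net change in average daily steps during the eighth week postquit date compared with average daily steps the week before the quit attempt", but a parenthesis there confines it to the HealthyCells+ arm.
- **Randomisation.** Under Study Randomization, "Participants will be stratified according to self-reported sedentary time at baseline", at three levels, and "Participants (n=60) will be randomized 1:1 in REDCap".
- **Wear time.** A valid day needs "a smartwatch that was worn for at least 10 waking hours" and at least 500 steps. The Analytic Plan repeats this: "Days with <500 steps or <10 hours of watch wear time (indicating nonwear time or recording error) will be excluded". It also requires at least 4 days of valid data. Otherwise "duration of smartwatch wear" appears only as a feasibility metric.
- **Incentives.** The HealthyCells+ section pays that arm alone for steps above 4000, for reaching 6000, and for each step-count photo. Payment starts on the quit date, runs for 4 weeks and resumes in week 8.

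**The concern.** There are two separate issues.

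The first is precision. A factor important enough to stratify on is a plausible predictor of steps, yet the stated comparisons leave it out. A raw change score also fixes the weight on the baseline week at 1, whereas ANCOVA estimates it. With 60 participants precision is scarce, and the article intends these comparisons as pilot data for a larger trial.

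The second is measurement. The watch counts steps only while it is worn, and the 10-hour rule sets a minimum, not a common wear time. The step contrast subtracts a prequit week, when nobody is paid for steps, from week 8, when one arm is. That arm has a reason to wear the watch longer in the second window. Any extra wear would add recorded steps without added walking, and a spurious signal could carry into the planning of the next trial.

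**Working it through.** **The plan's own figure.** N = 60 rests on feasibility recommendations. It agrees with 5 per month × 12 months = 60. The article gives no SD, correlation or power, so there is no precision figure to reproduce. The following are assumptions: SD of average daily steps 2500 (2000-3500 also examined), correlation r between the prequit week and week 8 of 0.3-0.8, and equal SDs in both weeks. Retention at the 75% floor leaves 60 × 0.75 = 45, or about 22 per arm.

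**Step 1: precision of the step contrast.**

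- Change-score variance: 2·SD²·(1 − r)
- ANCOVA residual variance: SD²·(1 − r²)
- Ratio, ANCOVA to change score: (1 + r)/2, which is 0.65, 0.75, 0.85 and 0.90 at r = 0.3, 0.5, 0.7 and 0.8

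With α = .20 the matching interval is 80%, so the half-width is 1.2816 × SD of the analysed quantity × √(2/22):

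| r | SD, change | SD, ANCOVA | Half-width, change | Half-width, ANCOVA |
|---|---|---|---|---|
| 0.5 | 2500 | 2165 | 966 | 837 |
| 0.7 | 1936 | 1785 | 748 | 690 |

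For a true difference of 1000 steps (the middle of the 500-1500 benchmark), power at α = .20 rises from 0.518 to 0.599 at r = 0.5 and from 0.667 to 0.718 at r = 0.7.

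**Step 2: validity.** A simulation with stratified allocation (2,000 runs per setting, SD 2500, 22 per arm) compared the change-score t test with ANCOVA including baseline steps and stratum. Empirical standard errors were about 761 versus 671 (r = 0.5) and 562 versus 531 (r = 0.7). Both estimators were essentially unbiased. Across 22 and 30 per arm, rejection under the null was 0.17-0.21 against a nominal 0.20.

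**Step 3: timing of the baseline week.** Study Enrollment places randomisation after the activation assessment. Study Randomization then has staff text each participant the code for the assigned app content, and the Overview has participants use the assigned app from one week before the quit date. The prequit week therefore follows randomisation. Suppose assignment shifts mean prequit steps by d and nothing else. The change score subtracts the whole of d, so its contrast is off by d. ANCOVA subtracts slope × d, and with equal SDs the slope is r, so its contrast is off by about r·d. At r = 0.5 that is half the error.

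**Step 4: wear time.** The article puts average steps at about 4000 per day. Over an assumed 12-16 worn hours the rate is 4000/12 = 333 or 4000/16 = 250 steps per hour. A stable wear difference between arms largely cancels in a change score; what matters is a between-arm difference in the change in wear on valid days. One hour of such a difference shifts the contrast by about 250-333 steps per day, and two hours by 500-667. The lower benchmark is 500, so one hour amounts to 250/500 = 50% to 333/500 = 67% of it.

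**Step 5: abstinence.** Only the stratum argument carries over. At the 20% benchmark there would be 60 × 0.20 = 12 abstinent participants over three strata and two arms. The documents give no association between sedentary time and abstinence, so no gain can be calculated.

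**The case against.** A reader might infer that the plan ignores baseline steps and wear time altogether. It does not. Baseline steps enter by subtraction, and wear is partly controlled by the 10-hour, 500-step and 4-valid-day rules.

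A reader might also infer that a false step benefit is to be expected in HealthyCells+. The documents do not show one. All participants are reminded daily to wear the watch, and both arms set and review activity goals. Added hours may carry fewer steps than the average hour. On wear alone, reaching 1500 steps at 333 per hour would need one arm to gain 1500/333 = 4.5 hours a day more than the other, which nothing in the article supports. The bias is possible, not demonstrated.

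The strongest technical objection is that the ANCOVA covariate would be measured after randomisation. That is correct and must be disclosed. It does not favour the planned analysis, because the change score depends on the same week more heavily (step 3).

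Finally, this is a feasibility trial, expressly not powered, reported in a condensed article, and covariates are often left to a fuller plan. That limits the weight of the point. It does not remove it, because the article itself fixes the tests and the change score.

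**Conclusion.** The concern holds as a loss of precision and a gap in the handling of wear time, not as an error that invalidates the comparisons.

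- **Steps.** Under the assumed SD of 2500 and 22 per arm, the planned interval is about 966 against 837 steps at r = 0.5, or 748 against 690 at r = 0.7: a reduction in half-width of about 13% or 8%. The variance ratio (1 + r)/2 does not depend on the assumed SD. The precision figures treat the prequit week as unaffected by assignment.
- **Abstinence.** The stratum is unused and the gain from using it is unknown.
- **Wear.** About 250-333 steps per hour of differential change, if 4000 steps are spread over 12-16 worn hours and added hours carry the average rate. Whether such a difference will arise cannot be judged from the article.

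The arithmetic on precision is firm once r is assumed. Confidence in the wear point is moderate.

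**What to change.** 1. **Reconcile first.** The postintervention outcomes section confines the step outcome to HealthyCells+, while the Analytic Plan compares the groups. Until this is settled no adjusted contrast is defined.
2. **Steps.** Analyse week-8 average daily steps by ANCOVA on arm, prequit-week steps and sedentary-time stratum. State that the prequit week follows randomisation, and add a sensitivity analysis adjusting only for the stratum and an activity measure taken before randomisation.
3. **Abstinence.** Replace the plain chi-square comparison with a stratum-adjusted risk difference (Mantel-Haenszel).
4. **Wear.** Report worn hours by arm and week, and prespecify a sensitivity analysis on steps per worn hour. Do not put wear in the main model: it is measured after randomisation and may itself be affected by arm, so adjusting for it could bias the effect.

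The main items are already collected: prequit steps, stratum and wear duration. The cost is a few lines of SAS and a small amount of extra reporting.

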To ensure accurate, objective measurement of step count, study staff will pair each participant’s Samsung smartwatch with a Samsung smartphone and create a unique Samsung Health account before shipping the study materials. The Samsung Health app integrates seamlessly with the smartwatch, allowing continuous step count tracking. These data sync automatically from the watch to the app, enabling real-time data capture. Throughout the intervention, the research team will periodically access each participant’s Samsung Health account to securely export step data, which will be saved as a file for analysis. Once participants return the phone and smartwatch, the study team will directly extract step data from the smartwatch to verify and complement the app-synced step data. This dual extraction process enhances data reliability, ensuring comprehensive and objective measurement of participants’ physical activity [102]. After this extraction, the phone and smartwatch will be reset to factory settings to prepare them for use with another participant, ensuring privacy and consistency across participants.

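### The between-group step comparison is complete-case only and leaves weeks 1 to 7 unused, so it can be biased if loss of watch data depends on steps and differs by arm

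*Protocol article*

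**What the plan says.** The Analytic Plan evaluates the change in average daily steps from the baseline week to week 8 with t tests between groups. Days with under 500 steps or under 10 hours of wear are dropped, and then "Participants must have at least 4 days of valid step count data to be included in the analyses". The rule does not say whether the 4 days apply to each week or to both together.

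The same paragraph analyses smoking twice: "an intention-to-treat analysis with missing data classified as smoking", and a completers-only analysis. Steps have no counterpart to the first.

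Under Postintervention Assessment and Treatment Outcomes, step data flow from the watch throughout the study: "The Samsung Health app integrates seamlessly with the smartwatch, allowing continuous step count tracking". They are exported periodically and extracted again from the returned watch. Weeks 1 to 4 and week 8 enter an exploratory logistic model for abstinence. Weeks 5 to 7 enter no stated model of average steps. The same section restricts the primary step outcome to the HealthyCells+ arm, while the Analytic Plan tests between groups.

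On payment, HealthyCells+ earns money for step photos and for steps, from the quit date through week 4 and again in week 8. HealthyCells earns nothing for steps. Both arms are paid for breath samples, abstinence, surveys, interviews and returning equipment.

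**The concern.** A t test on week-8 change uses only people who are still wearing the watch in week 8. Step pay requires a worn watch, it exists in one arm only, and it resumes in the endpoint week. Whether a participant has enough valid days could therefore be affected by the component that was randomised. If those who drop out of the step data are also the ones walking less, the comparison is made between differently selected survivors.

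A one-arm pre-post change has a similar weakness if loss within that arm is related to steps. This matters because one feasibility indicator is "observing a meaningful 500 to 1500 [106,107] average daily step increase at eighth week postquit date", and a change measured among survivors can distort that reading.

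The entry rule also leaves room for two analysts to include different people. A change score needs two weekly means. Read literally, 4 valid days in total would qualify, even 3 in one week and 1 in the other; read per week, 8 are needed.

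**Working it through.** **The plan's own figures.** There is no power calculation to reproduce. The enrolment figures agree: 5 per month x 12 months = 60. Retention of 75% leaves 60 x 0.75 = 45. If 15% of those lacked valid days (assumption), 45 x 0.85 = about 38 would be analysed.

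**Precision lost through dropout.** SE = SD x sqrt(1/n1 + 1/n2).
- From 30/30 to 22.5/22.5 the SE rises by sqrt(60/45) = 1.155, or 15.5%.
- An 18/27 split gives sqrt((1/18 + 1/27)/(2/30)) = 1.179. The imbalance itself adds only about 2%.
- Assume an SD of change of 2000 to 3500 and a 1000-step difference. At the plan's two-sided level of 0.20, power falls from 0.74-0.43 (30/30) to 0.65-0.37 (22.5/22.5).

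**Bias, assumption set A (no true arm difference).** 30 per arm; baseline mean 4500 (SD 1800); gain 600 (SD 1500) in both arms; weekly noise SD 900. Weekly dropout is 2% in HealthyCells+. In HealthyCells it is 5.5%, times 2.2 if recorded steps are below 4500 and times 0.5 otherwise. About 45 or 46 of 60 are analysed.
- Complete-case contrast (HealthyCells+ minus HealthyCells): -224 in 150 replicates (Monte Carlo error 564/sqrt(150) = 46). Larger runs gave -230 (5,000 replicates) and about -210 (3,000).
- Model on all weekly means: -16 in the small run and +2 in the 5,000-replicate run.
- SE: 592 to 531 and 600 to 537 in the larger runs, so the complete-case SE is about 12% larger (592/531 = 1.115; 600/537 = 1.117).
- HealthyCells survivors show a gain of about 830 where the truth is 600.

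**Bias, assumption set B (true difference 1000).** 30 per arm; weekly-mean SD 3000; correlation 0.6 of prequit steps with both the weeks 1-4 mean and week 8, and 0.7 between the weeks 1-4 mean and week 8; weeks 1-4 seen in everyone; 2,500 replicates per scenario. Retention is shown as HealthyCells/HealthyCells+.

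| Loss depends on | Retention (%) | Complete-case bias | Bias using weeks 1-4 and prequit steps |
|---|---|---|---|
| Nothing (completely at random) | 75/75 to 60/90 | +8 to +14 | +6 to +20 |
| Change seen in weeks 1-4, same in both arms | 75/75 | -2 to -7 | -8 to -9 |
| Change seen in weeks 1-4, same in both arms | 65/85, 60/90 | -225 to -573 | -6 to +32 |
| Change seen in weeks 1-4, HealthyCells only | 75/75 to 60/90 | -311 to -800 | -25 to +15 |
| Unseen week-8 change, same in both arms | 75/75 | -7 to -19 | -8 to -9 |
| Unseen week-8 change, same in both arms | 65/85, 60/90 | -429 to -884 | -262 to -555 |
| Unseen week-8 change, HealthyCells only | 75/75 to 60/90 | -513 to -1252 | -292 to -756 |

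The negative sign follows from assuming that participants with low change are lost more often, mainly from HealthyCells. That understates the HealthyCells+ advantage. Other assumptions could reverse it.

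**Where the precision gain comes from.** Under set B with loss completely at random at 75/75, the SE is 810 complete-case and 701 with the model (810/701 = 1.155). Where loss depends on weeks 1-4, the ratio is about 1.08 to 1.14. Part of this is adjustment for prequit steps. The change score has SD 3000 x sqrt(2 x 0.4) = 2683, so its SE is 2683 x sqrt(2/22.5) = 800. Adjusting complete cases for prequit steps gives 3000 x sqrt(1 - 0.36) = 2400 and 2400 x sqrt(2/22.5) = 716. In this set, then, most of the precision gain comes from prequit adjustment; the interim weeks matter mainly for bias.

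**The case against.** A reader might infer that unequal attrition between a paid and an unpaid arm biases the step contrast as a matter of course. The documents do not support that.
- Unequal loss alone does no harm: 60% against 90% retention at random gave +14 steps/day, within simulation error. Loss must also be related to steps, and in a way that differs by arm. The article gives no evidence of either.
- No passage pays for wear itself. Both arms are paid for other daily tasks and reminded daily to wear the watch. Steps sync passively, so a missing photo is not missing step data.
- Under the outcome definition limited to HealthyCells+, there is no between-arm primary contrast to bias.
- The near-zero bias of the model under loss depending on observed weeks follows from that assumption. With loss depending on unseen steps, about -260 to -760 steps/day remains.
- The sample size rests on guidance for trials that "prioritize assessing study processes, recruitment, retention, and intervention engagement rather than detecting statistically significant effects", and the duration of watch wear will be described.
- Counting 3 days plus 1 as valid is a strained reading, and mixed models and sensitivity analyses often sit in a separate analysis plan.

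Most of this stands, and it turns a claim of bias into a claim of risk. Three things remain. The complete-case t test and its entry rule are stated in the article, not left open. The same paragraph gives smoking an all-randomised analysis. And describing wear time helps interpretation without correcting the estimate.

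**Conclusion.** The concern holds as a risk of bias and a loss of precision, not as a demonstrated bias. The stated step comparison is complete-case, its 4-day rule names no period, and it leaves out seven weeks of watch data. Pay for steps in one arm only makes unequal validity plausible.

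If loss depends on observed weeks and differs by arm, the bias is about -200 to -800 steps/day under the assumptions shown, against a benchmark of 500 to 1500. It is nil if loss is random or acts equally in both arms. The complete-case SE is roughly 10 to 15% larger than under the fuller model. The SDs, correlations, dropout rates and mechanisms are all assumed, so these figures give a range and not an expected value.

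The feasibility purpose limits the consequences, but the change is worth making before the data are analysed.

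**What to change.** 1. State that 4 valid days are required in the prequit week and in each analysed week.
2. Reconcile the primary step outcome, defined for HealthyCells+ only, with the between-group test in the Analytic Plan.
3. Analyse weekly mean steps for all available postquit weeks in both arms with a mixed model: arm, week as categorical, arm-by-week and prequit steps. Take the week-8 arm contrast from it. Categorical week matters because step pay stops in weeks 5 to 7 and resumes in week 8.
4. Keep the complete-case t test as supportive, and report the numbers analysed by arm.
5. Add a simple sensitivity analysis for loss related to unobserved steps, for example shifting the assumed week-8 steps of those lost by a range of amounts in each arm.

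The cost is slightly more analysis work in the software already named, with no new data. The model relies on data being missing at random given the observed weeks, so it removes only the part of any bias that those weeks explain. That is why item 5 is needed.

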#### MHBC Intervention: HealthyCells+

In addition to the small financial incentives earned for biochemically verified abstinence, HealthyCells+ intervention participants will earn small incentives for increasing physical activity (ie, daily step count) during their quit attempt. Starting on their scheduled quit date, participants will be rewarded US $0.50 per 1000 steps for every step >4000 daily steps, and they will receive a US $2.50 bonus if they walk at least 6000 steps a day. These criteria were set based on research showing Black adults walk about 4000 steps per day on average [92]. Providing incentives above this threshold will ensure the incentive protocol will not reinforce a sedentary lifestyle, and a bonus for meeting the 6000-step per day goal will reinforce higher levels of daily physical activity and greater positive health benefits [92-100]. Participants will not be incentivized beyond 10,000 steps per day, consistent with previous research showing limited additional health benefits [93,95-100]. Therefore, the maximum amount participants can earn per day for daily steps will be US $5.50 (ie, US $3.00 for 10,000 steps +US $2.50 for step goal bonus), an amount that parallels the amount participants can earn at the fourth week postquit date for daily smoking abstinence.

Participants will self-report their daily step count via an assessment on the app home menu at the end of each day (based on self-reported typical time to bed). This assessment will also ask participants to upload a picture of their step count (captured by the smartwatch; Figure 4). To promote compliance, participants will receive US $1 for each successful photo upload (up to 7 submissions/US $7/wk). Participants will not earn incentives for their self-reported step count total if an image is not uploaded. Consistent with the incentive schedule for smoking cessation, participants will earn these incentives for increasing physical activity starting on the scheduled quit date up to 4 weeks postquit date. Incentives may also be earned during the final 7 days of the intervention period (eighth wk postquit date). To gain the maximum incentives for increasing physical activity (US $255.5), participants must submit all step count photos and take 10,000 steps daily during all eligible assessment weeks (ie, wk 1-4 and the eighth wk postquit date).

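### The step predictor in the exploratory logistic regression includes week 8, which is also the outcome window, so the model cannot show an impact of steps on quitting; the bias is modest

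*Protocol article*

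**What the plan says.** The Analytic Plan opens its last block modestly: "Exploratory analyses will examine the association between physical activity and smoking cessation success". It then becomes causal in tone: "Logistic regression analysis will evaluate the impact of average daily step count", and the predictor and outcome are given as "average daily step count based on all postquit assessment weeks (5 wk in total) on CO-verified 7-day point prevalence abstinence" at 8 weeks. A categorical version splits participants at a daily average of 6000 steps.

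The weeks are identified under MHBC Intervention: HealthyCells+, where the maximum step payment requires participants to "take 10,000 steps daily during all eligible assessment weeks (ie, wk 1-4 and the eighth wk postquit date"). The HealthyCells section lists the same weeks for breath samples. The position of the fifth week is also given: "Incentives may also be earned during the final 7 days of the intervention period (eighth wk postquit date").

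The outcome, under Postintervention Assessment and Treatment Outcomes, is "CO-verified, 7-day point prevalence smoking abstinence at 8 weeks postquit date".

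The completeness rule in the Analytic Plan is: "Participants must have at least 4 days of valid step count data to be included in the analyses". It says nothing about how those days are spread over the weeks.

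**The concern.** A predictor said to act on an outcome should be measured before it. Here the last of the five averaged weeks is the week over which abstinence is judged. If staying abstinent leads people to walk more, or relapse leads them to walk less, the week-8 steps carry the result of the outcome back into the predictor, and the regression reads this as steps helping people quit.

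The article's own Introduction makes that route plausible. It says that people who smoke report less activity, and that activity may take the place of smoking during a quit attempt.

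At stake is how an exploratory result is read when the larger trial is designed. The smartwatch data would equally allow a predictor that ends before the outcome week.

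**Working it through.** **1. Which weeks are averaged.** Weeks 1-4 plus week 8 give 4 + 1 = 5 weeks, the number stated, or 5 × 7 = 35 days. The payment total agrees. Photos at US $1 on every day of the nine-week period (9 × 7 = 63) plus step incentives of US $5.50 on 35 days give 63 + 192.50 = US $255.50, the stated maximum. Paying photos on the 35 days only would give 35 × 6.50 = US $227.50, which does not match.

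**2. Size of the overlap.** Week 8 is the final seven days of the intervention. A seven-day outcome assessed at the end of that week covers the same days. With complete data the shared part is 7/35 = 20% of the exposure window.

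**3. Dilution.** If abstinence raises week-8 steps by d per day, the five-week mean rises by d/5. The article treats a gain of 500 to 1500 steps a day as meaningful. Using that range for d gives shifts of 100 to 300 steps.

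**4. Simulation with no effect of steps on quitting.**
- From the article: 60 participants, or 45 at 75% retention (0.75 × 60); 20% abstinent; d of 500, 1000 or 1500.
- Assumed, because no figure is given: mean 5000 steps; between-person SD 1500 or 2500; within-person weekly SD 1000; weekly abstinence in weeks 1-4 of 90% for those abstinent at week 8 and 40% for the others.
- The .20 threshold is stated for comparisons between arms ("we will report all potential group differences with the α set at" .20). Applying it to the regression coefficient is an assumption.
- Method: logistic regression on steps/1000, complete step data, 800 trials per setting. The Monte Carlo standard error at 0.20 is √(0.2 × 0.8/800) = 0.014.

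| Where abstinence raises steps | Predictor | Median OR per 1000 steps | Share with p < .20 |
|---|---|---|---|
| Nowhere (d = 0) | Five weeks | 0.99-1.01 | 0.17-0.22 |
| Week 8 only | Five weeks | 1.01-1.13 | 0.17-0.30 |
| Week 8 only | Weeks 1-4 | 0.98-1.01 | 0.18-0.23 |
| Every abstinent week | Five weeks | 1.05-1.46 | 0.21-0.68 |
| Every abstinent week | Weeks 1-4 | 1.04-1.37 | 0.21-0.55 |

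For the five-week predictor with a week-8-only effect, the results by d are:
- 500 steps: OR 1.01-1.06, share 0.17-0.20
- 1000 steps: OR 1.03-1.10, share 0.20-0.23
- 1500 steps: OR 1.05-1.13, share 0.21-0.30

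Up to 1000 steps the share stays close to the nominal 0.20. The upper end of the range appears only at 1500.

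**5. A second check.** A t test of the five-week mean by outcome, with an assumed SD of 2000, rejects at .05 in about 5-6%, 9% and 14-15% of trials for d of 1000, 2000 and 3000. The last two values lie above the article's own range.

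**The case against.** The strongest reply is that this is a wording matter in a minor analysis. The block is labelled exploratory, and it opens and closes in terms of association. No primary outcome or feasibility benchmark rests on it. The effect of abstinence on steps is assumed in size and direction, and at 1000 steps a day it hardly moves the rejection rate. All of that stands, and it limits the weight of the point.

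It is also fair to say that moving to weeks 1-4 is no complete cure. Quitting begins on the quit date, so abstinence can raise steps in the early weeks too. The last row of the table shows the bias that then remains.

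The reply that an analysis plan would settle this carries less weight. The article does not leave the window open: it fixes five weeks and states what the model is to evaluate.

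Two further arguments should not be pressed. A reader might infer from the four-day rule that a five-week mean could rest wholly on week 8. The wording permits it, but the rule directly follows the baseline-to-week-8 comparison and may not have been written for this model. The case would also need someone with no valid days in weeks 1-4 who then wears the watch in week 8. A reader might also add that dropouts contribute early weeks only and are coded as smoking. That is a missing-data question, and the article does not say which of its two cessation analyses the regression uses.

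**Conclusion.** The overlap follows from the article's own definitions: one fifth of the exposure window, with complete data, is the outcome window. The order of steps and abstinence is therefore not secured, and *impact* is not supported. The version split at 6000 steps shares the fault if it uses the same average.

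The size is modest. A week-8-only reverse effect of 500-1500 steps a day gives a median odds ratio per 1000 steps of about 1.01-1.13 where the truth is 1. This depends on the assumed SDs and on abstinence raising steps at all, for which the article gives no figure.

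A reader might infer that the test of the trial's rationale is undermined. The documents do not support that: the central hypothesis concerns the two arms, is addressed by the randomised comparison, and does not use this model. A reader might also infer that a weeks 1-4 predictor would make the estimate causal. It would not: if abstinence raises steps in every abstinent week, the odds ratio is still 1.04-1.37. The change is worth making because it is cheap and removes a direct overlap.

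**What to change.** In the Analytic Plan, define the predictor of week-8 abstinence as average daily steps over weeks 1-4, both continuous and as 6000 or more, and apply the four-valid-day minimum within those weeks. If the five-week average is kept, report it only as a concurrent association.

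Replace *impact* with *association* throughout the block, and state that early abstinence may itself raise steps. A sensitivity analysis adjusting for arm and for abstinence during weeks 1-4 may be added.

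The cost is a short change of text and seven fewer days in the average (28 instead of 35), so slightly more noise. No new data are needed.
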